### Data collection

#### Primary outcome

Events of drunkenness are collected retrospectively after completion of the training on a weekly basis by the movisensXS app for the last 7 days. From these measurements, the time to first event of drunkenness is derived. In case of drunkenness events, quantitative measures of alcohol consumption are taken as numbers of units (bottles, glasses of various beverages) in an easy-to-answer manner. A weekly electronic measurement at 5 pm every Sunday proved to be feasible as did the research tool designed by the researchers on a flexible platform (movisensXS, Version 1.5.8, (movisens GmbH, Karlsruhe, Germany)).

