### Trial design

The study evaluates the effectiveness of a mindfulness-based intervention in preventing ATOD use in 11–17 years old boys with MBID with special focus on the consumption of alcohol. All adolescents fulfilling inclusion criteria will be randomised to either the intervention group or the active control condition (see Fig. 1). Persons who do not have experiences with alcohol will be invited to be part of a registry. With the registry data, we describe probabilities of starting to consume alcohol depending on personal risk factors. The study is designed as a prospective, randomised, controlled superiority trial proving our concept with two parallel groups. This randomised controlled trial (RCT) will be combined with a small add-on registry study. The first study arm comprises a mindfulness-oriented intervention, the second a sham intervention equal in length and dose, but different in content. Participants from both groups join a 6-week program conducted in one-to-one sessions. The intervention group receives a training containing mindfulness exercises and elements of drug prevention. The control group receives a training that contains exercises in health education instead of mindfulness. Participants in the registry receive no intervention and are measured at the same intervals and using the same measurement methods. The trial involves two assessment points (pre- and post-intervention) and a 12 months follow-up period with weekly measurements via the android app movisensXS starting at the last intervention session. Figure 1 shows the flow diagram of the current trial design.

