### Procedure

The study timeline is shown in Table 1. Boys who have consumed any alcohol within the last 12 months before initial assessment and who and their parents/caregivers have given written informed consent will be included in the study (t_0_ timing of enrolment). They undergo the baseline measures about the length of two sessions (t_1_ and t_2_). In case they do not fulfill the inclusion criteria of alcohol use they will be invited to be part of the non-intervention registry. In case they fulfill all inclusion criteria participants will be randomised to either the intervention group or control group in a 1:1 allocation ratio. A central randomisation list will be created with variable block lengths stratified by the recruitment locations school vs. clinics, outpatient clinics and practices. Enrolled participants will be randomized on the base of computer-generated random numbers provided by a research associate of the Institute of Medical Biometry and Epidemiology (IMBE) of the University Medical Center Hamburg-Eppendorf. This assistant is not involved in the practical implementation of the research project. After randomisation, participants get the training over six sessions. After completion of the treatment, participants take part in the post-measurements (t_3_-t_4_). During the post-measurement, the app (movisensXS) is installed on the smartphone of the participants. In case of compatibility problems, a smartphone is handed out to the test persons by the study staff. This smartphone will be only usable for the follow-up survey. For 12 months after intervention, every Sunday afternoon, participants get an app-based reminder and are asked to join the short follow-up survey. Here, they retrospectively report on their substance consumption for the last week directly on their smartphones (t_5_-t_57_) by answering questions via the app.

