### Plans for data collection

#### Follow up

##### Substance use

Our sampling method via movisensXS involves asking participants weekly about drunkenness events and the consumption of alcohol, tobacco and illicit drugs. For binging events, they will be asked for the timing, quantity and experience. The questioning takes a maximum of 3 min. It starts the first week after the intervention and should be carried out weekly for a total of 52 weeks.

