##### Substance use

The Timeline Followback (TLFB) is a calendar method in which participants are asked retrospectively about their consumption of alcohol, nicotine, cannabis and other drugs, establishing a 30-days-before baseline and a post-measurement calendar [49].

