### Statistical analysis

#### Sample size

For the primary outcome “time to first event of drunkenness”, we calculated the sample size for a logrank test comparing the intervention and control group. In the literature, we did not find data referring to students with MBID for precise estimating of the base rates of survival. Hence, we refer to the European School Survey Project on Alcohol and other Drugs (ESPAD, see Introduction). ESPAD-data indicates that about 60% of students report at least one event of drunkenness during the last year, which makes an event-free survival rate of 0.4 in the control group. In the absence of evidence-based assumptions on the effectiveness of the intervention, we estimate that the intervention will drop down the events of drunkenness from a base rate of 60 to 28%, which corresponds to an event-free survival rate of 0.72 in the intervention group. This leads to a hazard ratio of 0.36. With a power of 80% and a significance level of 5% (two-sided hypothesis), we need an overall sample size of 82 participants (41 participants per group) to detect this difference. We assume that we lose 30% of the participants in each group during the study duration. These observations are censored. Furthermore, we expect no one to switch groups. The study is planned without accrual period.

For the most important secondary outcomes “quantity of alcohol units /number of tobacco cigarettes”, we can show median effects of .65 in terms of Cohens d with this sample size and with a type I error of α = .05 (two-sided hypothesis), a power of 1-β = .80 and a correlation between baseline and follow-up of r = .50. The sample size calculation was conducted with PASS 15 based on the modules “Logrank Tests” and “Analysis of Covariance”.

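### No back-fill is described for skipped weekly surveys, so a first drunkenness in a skipped week is lost or dated too late

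*Protocol article*

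**What the plan says.** Under Primary outcome, the Protocol article states: "Events of drunkenness are collected retrospectively after completion of the training on a weekly basis by the movisensXS app for the last 7 days". It continues: "From these measurements, the time to first event of drunkenness is derived". The Procedure section gives the same look-back: "they retrospectively report on their substance consumption for the last week directly on their smartphones". The follow-up text on substance use says the survey "should be carried out weekly for a total of 52 weeks".

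Other data sources do not cover the follow-up year. Trial design states: "The trial involves two assessment points (pre- and post-intervention) and a 12 months follow-up period with weekly measurements". The calendar interview serves baseline and post-measurement only, "establishing a 30-days-before baseline and a post-measurement calendar".

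On missing data, the Sample size section assumes that 30% of each group is lost and adds: "These observations are censored". That sentence concerns boys who leave the study. The statistical methods section describes imputation only for the secondary linear mixed model. Nothing addresses a boy who skips one or more Sundays and then answers again.

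**The concern.** Each week of follow-up is covered by exactly one survey. If that survey is skipped, the next one starts its look-back after the skipped week has ended. The recorded first event is then the first event in an answered week.

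Two things can happen to a first drunkenness in a skipped week. If a later drunkenness falls in an answered week, the boy counts as having an event, but too late. If none does, he counts as event-free. Either way the primary endpoint depends partly on how regularly boys answer the app. The trial was sized on about 31 events, so it has few to spare.

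An analysis plan can choose how to treat a gap, but it cannot restore an event that nobody asked about. The issue therefore lies in data collection, which this document does fix.

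**Working it through.** **Inputs from the document (Sample size).** Event-free rates at 12 months of 0.40 (control) and 0.72 (intervention), 41 boys per arm, 30% loss per arm, two-sided 5%, power 80%.

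**Reproducing the plan.** Hazards per year: control −ln 0.40 = 0.916; intervention −ln 0.72 = 0.3285; ratio 0.3285/0.916 = 0.36, as stated. Loss hazard −ln 0.70 = 0.357. The probability of an observed event is λ/(λ+0.357) × (1 − exp[−(λ+0.357)]):
- control 0.518, intervention 0.238
- expected events 41 × (0.518 + 0.238) = 31.0

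Schoenfeld's formula needs 31 events at a hazard ratio of 0.36, and 31/0.378 = 82. The planned size reproduces. Power at 31 events is 81.5% by Schoenfeld and 79% by the Lakatos method.

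**Are gaps likely?** The weekly response rate is not given. If answers were independent from week to week, the chance of completing all 52 surveys would be 0.99^52 = 59%, 0.95^52 = 7% or 0.90^52 = 0.4%. Clustering of misses within boys would raise these figures. Some gaps should still be expected.

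**Equal response in both arms.** Assume response probability p, misses unrelated to drinking, later drunkenness at the same rate as the first, and skipped weeks counted as event-free. The observed hazard is then pλ. With the 30% loss kept in:

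| p | Expected events | Power (Lakatos) | Power (Schoenfeld) |
|---|---|---|---|
| 1.0 | 31.0 | 79% | 81% |
| 0.9 | 28.7 | 75% | 79% |
| 0.7 | 23.8 | 67% | 71% |
| 0.5 | 18.1 | 54% | 59% |

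At p = 0.7 the event probabilities are 0.406 and 0.174, and 41 × 0.580 = 23.8. Both hazards shrink by the same factor, so the ratio stays at 0.36. In a simulation of 200,000 boys per arm over 52 weeks, without loss, detected control events were dated on average 0.6, 1.9 and 3.2 weeks late at 90%, 70% and 50% response.

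Other recurrence patterns move the planned ratio modestly. At 70% response it is 0.40 if drunkenness never recurs and 0.34 if it recurs at three times the first rate. Under a true null it stays at 1.0.

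**Different response by arm, true hazard ratio 1.0.** Same simulation, without loss, for an assumed 20-point difference:

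| Recurrence | 90% control, 70% intervention | 70% control, 90% intervention |
|---|---|---|
| none | 0.71 | 1.40 |
| same rate | 0.78 | 1.30 |
| three times the rate | 0.87 | 1.17 |

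The same-rate row agrees with direct arithmetic: 0.7/0.9 = 0.78 and 0.9/0.7 = 1.29. In the first column, the approximate chance of a significant result favouring the intervention is 18%, 13% and 7%, against 2.5% nominal.

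**The case against.** - **The article may omit app detail.** The form is not reproduced, and the text does not say whether a prompt can be answered late or whether staff contact non-responders. This is fair. The point therefore rests on the recall window, which is stated twice, and on the absence of any described recovery.
- **Handling of gaps belongs in an analysis plan.** True of the censoring rule. But no rule recovers unasked data. For example, censoring at the first gap with 10% of weeks missed independently would leave 0.9^13 = 25% of boys without a gap by week 13.
- **Safeguards exist.** The Sunday survey was found feasible, takes at most three minutes, comes with a reminder, and a phone is lent where needed. These support good response, but no rate is reported.
- **The arms are matched.** Setting, dose, duration, drug education and app are the same in both.
- **Double counting.** Boys who stop answering may be part of the planned 30% loss, so adding a further 30% of missed weeks may overstate the cost.

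A reader might infer that the plan biases the trial towards the intervention. The document does not support that. Nothing in it suggests that one arm will respond less, and the direction could be either. A reader might also infer that heavy weekends cause missed Sundays. That is plausible and would make the missingness informative, but the document says nothing on it. Nor does "These observations are censored" show that skipped weeks are censored, since it refers to boys lost from the study.

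**Conclusion.** The point holds as a weakness in how the primary endpoint is collected. As described, a first drunkenness in a skipped week is lost, or dated late if another is reported.

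The probable cost is lost events and power. At an assumed 70% response in both arms with same-rate recurrence, events fall from about 31 to 24 and power from about 80% to 67–71%. At 90% response the loss is small. Material bias in the hazard ratio is conditional: it needs response that differs by arm or depends on drinking, and its direction is unknown. The ranges of 0.71–0.87 and 1.17–1.40 illustrate an assumed 20-point difference under the null and are not forecasts. Every response and recurrence rate here is an assumption. The change is worth making because it is cheap and because weeks already skipped become harder to recover as time passes.

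**What to change.** 1. Keep the 7-day question for a boy who answered the previous week. After a missed survey, have the next one ask about the whole period since the last completed survey, with a week picker, and take the event week from that report.
2. Where a gap stays unresolved, add a sensitivity analysis that treats the event as interval-censored between the last negative and the first positive report.
3. Report weekly response by arm, so that readers can judge whether differential response is a real threat.

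The cost is a change to the app form and a short addition to the analysis. The downside is longer recall with some dating error, which matters in boys with limited cognitive ability. It falls only on the recovered weeks, for which there would otherwise be no information.

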#### Secondary and other outcomes

Secondary outcomes include self-reported alcohol use during the first year after intervention as a quantitative measure of consumption taken on a weekly basis using a smartphone-based research tool.

For all participants, the number of cigarettes will be inquired weekly.

Furthermore, emotion regulation, neurobehavioural self-regulation, trait mindfulness, psychological attributes, perceived stress and health-related quality of life and will be measured before and after the intervention. In case of drunkenness events, the weekday of the event and event-related social networks will be recorded. The consumption of illicit drugs of any kind will be asked for on a weekly basis. Sociodemographic data on the adolescent’s family contain consumption habits in the parental household (specific target variables and measurements are listed in Table 1).

### Plans for data collection

#### Follow up

##### Substance use

Our sampling method via movisensXS involves asking participants weekly about drunkenness events and the consumption of alcohol, tobacco and illicit drugs. For binging events, they will be asked for the timing, quantity and experience. The questioning takes a maximum of 3 min. It starts the first week after the intervention and should be carried out weekly for a total of 52 weeks.

#### Pre/ post measurements

Most of the measures taken are harmonised throughout the projects of the IMAC-consortium [44–47].

##### Sociodemographics

Items are based on the questionnaire of the Statistisches Bundesamt for recording sociostructural survey characteristics in the population [48].

##### Substance use

The Timeline Followback (TLFB) is a calendar method in which participants are asked retrospectively about their consumption of alcohol, nicotine, cannabis and other drugs, establishing a 30-days-before baseline and a post-measurement calendar [49].

##### Family risk factors

In order to record risky alcohol consumption, addiction or abuse, the alcohol consumption of parents/caregivers is measured with the help of a German translation of the 10-item Alcohol Use Disorders Identification Test (AUDIT) [50], of which one item will be used. Health-relevant data on smoking, sport, eating and sleeping behaviour in the family will be collected via a self-authored items.

##### Mindfulness

The Mindful Attention Awareness Scale-Adolescents (MAAS-A) for young people between 14 and 18 years of age contains 15 items for the assessment of dispositional mindfulness [51]. The questionnaire takes a maximum of 10 min with a good internal consistency (alpha = .82) and retest reliability (r = .79).

##### Personality

Substance Use Risk Profile Scale (SURPS) is a 23-item self-assessment questionnaire that includes four personality risk factors for substance abuse (impulsiveness, sensation-seeking, anxiety sensitivity, and hopelessness) [52].

##### Intelligence

The Wechsler Nonverbal Scale of Ability (WNV) is a non-verbal general cognitive ability assessment for children, teenagers, and young adults aged 4 to 21. The brief version lasts requires 15–20 min and consists of the two subtests matrices and spatial span [53]. It will be used in cases when no sufficient information about intelligence level or schooling can be found.

##### Neuropsychological testing

This neuropsychological computer-based testing includes three separate test paradigms.
Stop-Signal Task for recording response inhibition.Monetary Incentive Delay Task measuring reward anticipation.Cambridge Gambling Task assessing decision-making and risk-taking behaviour.

The neuropsychological test battery takes about 40 min and was designed by a subproject of the IMAC consortium [54].

##### Perceived stress

The short form of the Perceived Stress Scale (PSS-4) is a four-item well-validated self-assessment of perceived stress during the last month [55].

##### Emotion regulation

The Difficulties in Emotion Regulation Scale (DERS; Gratz & Roemer, [56], German version Ehring et al., [57]) is a well-validated and reliable self-report measure of emotion regulation and dysregulation (Cronbachs alpha = .95, split-half reliability = .96) targeting the 11–17 year olds. In the current trial, we are focusing on 3 of the 5 subscales, (1) Difficulties engaging in goal-directed behaviour (goals), (2) Impulse control difficulties (impulse) and (3) Limited access to emotion regulation strategies (strategies).

##### Health-related quality of life

The health-related quality of life of children and adolescents will be assessed with the Kidscreen-10 Index by means of self-disclosure and external assessment by parents in a pre measurment [58]. The 10-item-questionnaire provides a good internal consistency reliability (Cronbach’s Alpha = .82) and a moderate retest reliability (r = .73).

##### Influence of peers

A small self-developed network inventory asks for peer influences on alcohol and tobacco consumption. Three name-generators of most important friends are explored in greater detail for descriptive and injunctive social contagion, selectivity, and importance.

##### Psychopathological symptoms

The German version of the Strengths and Difficulties Questionnaire (SDQ, [59]; German version by Woerner [60, 61], is suitable for children and adolescents between 3 and 17 years of age. The test comprises 25 positive and negative attributes of the 5 subscales emotional symptoms, conduct problems, hyperactivity/inattention, peer relationship problems and prosocial behaviour. The same 25 items are included in a questionnaire version to be filled in by the parents.

##### Impact of the Covid-19 situation

Corona-related stress perception is measured with a short adaptation of CoRonavIruS Health Impact Survey (CRISIS) V0.1 [62]. The questionnaire consists of 12 items in the parent version and 9 items in the children version.

##### Prenatal androgen exposure

During the intrauterine period, androgen exposure organises the brain with lifelong neurobiological and behavioural effects. There is multi-level evidence that higher prenatal androgen exposure increases the risk for substance use disorders in later life [63–66] and also affects mindfulness [67] and the body mass index [68]. Within the projects of the IMAC-Mind Consortium, the participants’ second-to-fourth-finger length ratios (2D:4D), a proxy of prenatal androgen exposure, will be quantified via optical measurement.

### Statistical analysis

#### Sample size

For the primary outcome “time to first event of drunkenness”, we calculated the sample size for a logrank test comparing the intervention and control group. In the literature, we did not find data referring to students with MBID for precise estimating of the base rates of survival. Hence, we refer to the European School Survey Project on Alcohol and other Drugs (ESPAD, see Introduction). ESPAD-data indicates that about 60% of students report at least one event of drunkenness during the last year, which makes an event-free survival rate of 0.4 in the control group. In the absence of evidence-based assumptions on the effectiveness of the intervention, we estimate that the intervention will drop down the events of drunkenness from a base rate of 60 to 28%, which corresponds to an event-free survival rate of 0.72 in the intervention group. This leads to a hazard ratio of 0.36. With a power of 80% and a significance level of 5% (two-sided hypothesis), we need an overall sample size of 82 participants (41 participants per group) to detect this difference. We assume that we lose 30% of the participants in each group during the study duration. These observations are censored. Furthermore, we expect no one to switch groups. The study is planned without accrual period.

For the most important secondary outcomes “quantity of alcohol units /number of tobacco cigarettes”, we can show median effects of .65 in terms of Cohens d with this sample size and with a type I error of α = .05 (two-sided hypothesis), a power of 1-β = .80 and a correlation between baseline and follow-up of r = .50. The sample size calculation was conducted with PASS 15 based on the modules “Logrank Tests” and “Analysis of Covariance”.

#### Statistical methods for primary and secondary outcomes

The descriptive statistics will be presented separately for every group and for the total sample. The primary and secondary analysis will be based on the intention-to-treat population, which includes all participants randomised. For the primary outcome “time to first event of drunkenness”, a logrank test will be calculated to compare group differences in survival curves. The resulting statistical test for group comparison will be performed two-sided at the 5% significance level. The analysis will be repeated in the per-protocol population. In an additional analysis, we will extend this time-to-event-analysis to a Cox regression to adjust our results for the following covariates: intelligence, age, mindfulness, mental health, and family risks. If the event “drunkenness” occurs frequently enough in the individual participant, for the secondary analysis we will use an appropriate extension of the Cox model to deal with recurrent events and a Poisson regression using the count of the events as the dependent variable. For the most important secondary outcomes, change from baseline of the number of alcohol units and change from baseline of the number of cigarettes, a baseline-adjusted linear mixed model will be calculated for each outcome with participants as a random effect and group (intervention vs. control), time and recruitment location (schools vs. clinics, outpatient clinics, and practices) as fixed effects, and the respective baseline value as a covariate. The time by group interaction will be tested, and if the interaction is not significant, the interaction will not be included in the model. In this model, missing values will be directly imputed to enable an intention-to-treat analysis, which results in unbiased estimators under the missing-at-random-assumption. For further secondary outcomes (neuropsychological testing and questionnaires), a baseline adjusted analysis of covariance will be determined with the respective change from baseline to post-intervention as a dependent variable, group and recruitment location as independent variables, and the respective baseline value as a covariate. The analysis of all secondary outcomes will be performed in an exploratory manner. Interim analyses are not planned. Exploratory analyses will be performed for possible intervening factors, such as neurobehavioural parameters, mindfulness (trait) or quality of life. The analysis of the registry study will be performed in an exploratory manner. Probabilities of starting to consume alcohol will be described descriptively.

Standard statistical software as STATA (Version 16.0 or newer), R (Version 4.0.3 or newer), SAS (Version 9.4 or newer) or SPSS (Version 25 or newer) will be used for the statistical analyses.

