### Specific objectives of the study

The study aims to provide initial evidence that mindfulness can play an important role in preventing boys with MBID from consuming alcohol, tobacco and other drugs (ATOD), with alcohol being the focus of interest. Furthermore, we like to target and evaluate the role of bio-behavioural factors in improving addiction-related outcomes. The effectiveness of the intervention is evaluated in a randomised controlled trial with an active control condition and weekly follow-ups over a period of 12 months to test the following hypotheses: (1) The intervention is more effective than the active control condition with regard to time between the end of the training and the first event of drunkenness within 1 year after treatment (primary outcome). More precisely, the time span between treatment and first drunkenness event should be longer for the intervention group when compared to the control group. (2) Participants from the intervention group show stronger decrease in ATOD consumption (secondary outcome). (3) The effectiveness of the intervention is associated with changes in the neurobiological parameters of self-regulation, changes in mindfulness, psychopathological symptoms (strengths and weaknesses), and changes in perceived stress and health-related quality of life. Other parameters like reward anticipation, decision making, and impulse control will be examined on an exploratory basis (for details see Statistical analysis section below).

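### The primary outcome is recorded only by an app installed after training, so the intention-to-treat test is in effect limited to randomised boys who received the app

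*Protocol article*

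**What the plan says.** The section on statistical methods defines the analysis set: "The primary and secondary analysis will be based on the intention-to-treat population, which includes all participants randomised". For the primary outcome, "a logrank test will be calculated to compare group differences in survival curves", and then "The analysis will be repeated in the per-protocol population".

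The first hypothesis, under Specific objectives, measures time from the end of training to the first drunkenness within one year. Under Primary outcome, "Events of drunkenness are collected retrospectively after completion of the training on a weekly basis by the movisensXS app", with a look-back of seven days. Under Procedure, the order is baseline sessions t1 and t2, randomisation, six sessions, then the post-measurement (t3 and t4) once treatment is complete. There, "During the post-measurement, the app (movisensXS) is installed on the smartphone of the participants".

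On losses, the Sample size section says: "We assume that we lose 30% of the participants in each group during the study duration. These observations are censored".

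**The concern.** Both the time origin and the only named source of the primary outcome come after randomisation and after about six weeks of arm-specific training. A boy who is randomised but never attends the post-measurement gets no app and gives no weekly report. For a boy who stops training early, the article does not say whether he is still followed, and the end of training, which is his time zero, is undefined.

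Two things are at stake for the single confirmatory test. First, boys without the app supply no events, so the test has less information than a calculation in which all 82 boys start the clock. Second, a set formed after randomisation loses the protection of randomisation if early loss differs between arms and is related to drinking risk. The arms differ in content (mindfulness exercises against food, sport and sexuality), so unequal attendance is possible, though the article gives no evidence of it.

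**Working it through.** **Inputs from the Sample size section.** Event-free rates 0.40 (control) and 0.72 (intervention), two-sided 5%, power 80%, 82 boys (41 per arm), 30% loss per arm, no accrual period.

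**Step 1: reproduce the plan.**
- HR = ln(0.72)/ln(0.40) = 0.3585, stated as 0.36.
- Schoenfeld events: 4(1.960 + 0.842)²/(ln HR)² = 29.8, so 30. Freedman events: 36, and 36/0.44 = 81.8, so 82 with no loss (0.44 is the mean of 0.60 and 0.28).
- With exponential loss of 30% over the year, the event probability per arm is λ/(λ+μ) × (1 − exp(−(λ+μ))), with λ = −ln S and μ = −ln 0.70. This gives 0.518 and 0.238, mean 0.378. Then 30/0.378 = 79.4 boys, and 82 × 0.378 = 31.0 expected events.
- A Lakatos-type calculation with the same loss gives 78.8% power at 82. A simulation with weekly ties gives 80%. The stated 82 is reproduced closely enough.

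**Step 2: what censoring at time zero does.** The logrank statistic sums observed minus expected events over the event times. A boy censored at time zero is in no risk set at any event time, so he adds nothing to either sum. In one simulated data set, with 15% of boys lost at the start, the test gave chi-square 6.587 and p = 0.0103 both with those boys included and with them left out.

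**Step 3: power under assumed early loss.** The article gives no rate of loss before installation, so every row after the first is an assumption. The Lakatos-type calculation starts with 82(1 − x) boys. Where x lies inside the 30%, later loss is 1 − 0.70/(1 − x).

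| Lost before app (x) | Later loss | Expected events | Power at 82 | N for 80% |
|---|---|---|---|---|
| none | 30% | 31.0 | 78.8% | 85 |
| 5%, inside the 30% | 26.3% | 30.1 | 77.6% | 88 |
| 10%, inside | 22.2% | 29.2 | 76.4% | 90 |
| 20%, inside | 12.5% | 27.2 | 73.6% | 96 |
| all 30% | none | 25.3 | 70.5% | 104 |
| 10%, on top of the 30% | 30% | 27.9 | 74.5% | 94 |
| 20%, on top | 30% | 24.8 | 69.4% | 106 |

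The separate simulation agrees: 77% and 74% for 10% and 20% inside, 71% for all 30% early, and 75% and 69% for 10% and 20% on top.

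**Step 4: type I error under assumed early loss, with no true effect.**
- With log-hazard SD 1.0 to 1.5 between boys and higher-risk boys more likely to leave (3,000 runs per scenario): 5% to 6% when both arms lose 10%, 6% to 7% at 10% against 20%, and 8% to 12% at 5% against 25%.
- With 30% high-risk boys and early loss only among them (4,000 runs): 4.9% when both arms lose 15% and high-risk boys have twice the hazard. With three times the hazard, it is 10.2% at 5% against 25% and 15.7% at the extreme of 0% against 30%. With no loss (twice the hazard) the simulation gave 5.7%, so differences of under a point are not meaningful.

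**Step 5: boys who stop training early.** The Trial design section starts weekly measurement at the last intervention session, but Procedure installs the app at the later post-measurement. Read literally, a boy whose last session was the second would start his clock weeks before he could have the app, and the app looks back only seven days.

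**The case against.** A reader might infer that the intention-to-treat analysis cannot be run at all. The article does not support that. It says lost boys are censored, and the test can be computed on 82 boys with some censored at time zero. The defect is that this censoring carries no information.

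A reader might also infer that every boy who leaves training drops out of the primary test, making it a completer analysis. That is not stated. Procedure describes the ordinary path, and nothing bars a boy who misses sessions from the post-measurement or the app. The planned per-protocol repeat suggests that the authors expect some boys with data who did not follow the protocol, and a full protocol, not shown, may set out their follow-up. The point is firm only for boys who never reach the post-measurement; for the others, the article gives neither a route nor a time zero.

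A third tempting reading is that the mixed-model claim for alcohol units and cigarettes fails as well. The article says "In this model, missing values will be directly imputed to enable an intention-to-treat analysis", but makes unbiasedness conditional on data missing at random, and a likelihood model under that assumption does not need a weekly value from every boy. The assumption may be doubted, but the claim is not wrong as written, and those analyses are exploratory.

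Finally, the stated 30% covers the whole study and may already include early loss. The arms match in setting, dose, duration and homework, with a voucher for each session, so strongly unequal loss is a possibility and not a prediction. All of this stands. It limits the size of the problem, but it does not supply primary-outcome data for a boy without the app.

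**Conclusion.** The concern holds in limited form. As described, data collection does not secure the stated analysis set for the confirmatory test: a randomised boy who misses the post-measurement is counted in name only. This is more than detail left to an analysis plan, because no analysis can recover reports that were never collected.

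The size is unknown. If early loss falls within the planned 30%, the cost is modest: about one to five points of power from a base of 78.8%, for 5% to 20% lost early. It reaches eight to nine points if all 30% goes early or if 20% comes on top. These figures assume that early loss is unrelated to risk and that hazards are constant. Material inflation of type I error needs loss that is both strongly unequal between arms and related to drinking risk; equal loss leaves it near 5%. The hazard ratio of 0.36 and the 82 boys are not in dispute.

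**What to change.** Change three statements in the protocol.

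1. Install the app, or hand out the study phone, at baseline session t2, before randomisation. It can stay silent until time zero.
2. State that every randomised boy stays on the Sunday survey whatever his attendance at training or at the post-measurement.
3. Set time zero in both arms at the scheduled date of the sixth session, which exists for every randomised boy.

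Report by arm the number of boys with no app data; they remain censored at time zero.

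The cost is small: an existing visit is used about six weeks earlier, with no extra boys. Some phones will go to boys who later leave, and the time origin is reworded from the actual to the scheduled end of training. The change does not remove bias from risk-related loss after installation.

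If the sponsor prefers not to do this, the primary set should be named modified intention-to-treat (randomised boys who received the app), pre-app loss reported by arm, and power stated on that number.
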